#### Mediation Analysis

To determine whether the improvements in patient outcomes are mediated by patient self-efficacy and social support, we will employ the approach originally described by Baron and Kenny and more recently further developed by others [44-48]. In addition to the linear models relating outcomes to study group, we will fit two additional models relating mediator to the study group, and the model relating the outcome to the mediator and study group. To establish mediation, the study group effect has to be significant in all but the last model. If in the last model the study group effect is not significant, then we will conclude that complete mediation has occurred. If in the last model the study group effect is reduced, but is still significant, then we will conclude that partial mediation has occurred. To test for mediation, Sobel's test will be carried out, and percent of variation in outcomes mediated by patient or caregiver mediators will be determined [49-51].

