The current protocol describes an ongoing randomized trial designed to address these gaps in the literature by developing and evaluating an intervention that provides cancer patients and caregivers with the information they need to make effective management decisions, decrease symptom burden, and improve patient and caregiver outcomes. The study was funded by the VA Health Services Research and Development Service and began October, 2009. The trial will be completed in August 2013.

The intervention uses a Web-enabled program to alert caregivers of patients' symptoms and provide them with a framework for identifying problems, receiving structured advice, and following up to assist the patient in manage symptoms while receiving chemotherapy. Specifically, the intervention includes weekly, automated telephonic symptom assessment with self-management support calls to patients paired with Web-based caregiver alerts that include customized advice. The study will enroll 300 patients with solid tumors undergoing chemotherapy identified from two Department of Veterans Affairs (VA) outpatient oncology clinics. Patients are recruited along with an informal caregiver willing to play a limited role in assisting the patient with symptom management. The impact of the intervention will be evaluated relative to a control arm in which patients receive automated telephonic symptom assessments and self-management advice without any involvement of their identified caregiver. Thus this is one of the few rigorously designed interventions that tests the value added impact of engaging informal caregivers in symptom management for patients with cancer. Specific study hypotheses are as follows:

*Hypothesis 1a: Patients receiving automated telephonic symptom assessment and management advice, with Web-based feedback to inform and engage a caregiver, will report less frequent and less severe symptoms at 10 and 14 weeks when compared to patients receiving automated telephonic symptom assessment and management advice alone. Intervention-group patients will also report better physical function, fewer outpatient visits and hospitalizations related to symptoms, and greater adherence to chemotherapy*.

*Hypothesis 1b. The effect of the intervention on symptom severity, physical functioning, and utilization of services will be partially mediated by improved patient self-efficacy and actualized social support*.

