#### Self-efficacy

(source: patient baseline and 10 week surveys). The Cancer Behavior Inventory

(CBI) Version 2 will be employed to measure patient self-efficacy. The CBI has an internal validity of .94 and covers 7 aspects of self-management, including: maintenance of activity and independence, seeking and understanding medical information, stress management, coping with side effects of treatment, accepting cancer/maintaining positive attitude, affective regulation, and seeking support [37].

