### Data Analysis

#### Sample Size Calculation

Testing the primary outcome using two sided t-testing will require at least 224 dyads (patients and caregivers) to complete the study (112 per arm). This sample size affords 80% power to detect a difference as small as 0.33 standard deviations in mean summed symptom severity (Hypothesis 1) and social support (Hypothesis 2) between arms using 0.05 as the level of significance. This consistent with standards for clinical relevance and those seen in similar interventions [26,42]. Moreover, this sample size is sufficient to accommodate longitudinal analyses with repeated measures. To account for 25% attrition (consistent with prior trials of ATSA) and ensure that 112 dyads in each group are available for analysis, the goal is to enroll 300 dyads in the trial [26].

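### The mediation rule reads a non-significant direct effect as complete mediation, in a trial sized only for the total effect and hypothesising partial mediation

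*Protocol article*

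**What the plan says.** Hypothesis 1b (protocol article, Background) is that the effect on symptom severity, physical functioning and service use "will be partially mediated by improved patient self-efficacy and actualized social support".

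The Mediation Analysis section tests this with the causal-steps (Baron-Kenny) method. There are three models: outcome on group, mediator on group, and outcome on mediator and group. The gate is "To establish mediation, the study group effect has to be significant in all but the last model". Two verdicts follow from the last model:

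- Complete: "If in the last model the study group effect is not significant, then we will conclude that complete mediation has occurred".
- Partial: "If in the last model the study group effect is reduced, but is still significant, then we will conclude that partial mediation has occurred".

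The section then adds: "To test for mediation, Sobel's test will be carried out, and percent of variation in outcomes mediated by patient or caregiver mediators will be determined". Neither of these quantities enters the choice between complete and partial.

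The Sample Size Calculation section sizes the trial for the difference between arms, that is, the total effect: 0.33 SD, 80% power, 112 completers per arm. The article states no power for the direct effect, and the verdict rule uses neither a margin nor a confidence interval for it.

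**The concern.** A non-significant direct effect has two explanations: there is no direct effect, or the trial is too small to detect the one that exists. The rule always picks the first.

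If Hypothesis 1b is true, and the direct and indirect effects point the same way, the direct effect is smaller than the total effect by definition. Power for it is then below the power for the total effect, which is the only effect the trial is sized for. A correct verdict of partial mediation needs that smaller effect to reach significance. When it does not, the trial reports complete mediation, and its own hypothesis is set aside for a stronger claim that the data do not support.

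What is at stake is the conclusion on mechanism. A verdict of complete mediation says that self-efficacy or social support carries the whole benefit and that no other pathway matters.

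**Working it through.** **Inputs from the article.** 112 per arm; "Testing the primary outcome using two sided t-testing will require at least 224 dyads"; "using 0.05 as the level of significance"; total effect 0.33 SD; 80% power (all Sample Size Calculation). The gate and verdict rule are as in Mediation Analysis.

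**Assumed inputs.** The article gives neither the effect of group on the mediator (a) nor the direct share of the total effect. I take a = 0.33 or 0.50 SD and vary the share.

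**Step 1: the plan's own figure.** Two-sided, n per arm = 2(1.96 + 0.842)² / 0.33² ≈ 144, or 145 with the t correction. So 112 per arm does not reproduce. Power at 112 is 69.5%, and the effect detectable with 80% power is 2.80 × √(2/112) ≈ 0.374 SD. A one-sided test would need 114. This is a separate issue. Here it only means that both 0.33 and about 0.375 SD should be tried as the total effect.

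**Step 2: power for the direct effect.** In a simple two-sample comparison, SE = √(2/112) = 0.1336. If half of 0.33 SD is direct, 0.165 / 0.1336 = 1.235, and power is about Φ(1.235 − 1.96) = Φ(−0.725) ≈ 23%. If 75% is direct, power is 46%. With a total of 0.374 SD the two figures are 29% and 56%.

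In the model containing the mediator, SE ≈ √(2/112) × √(1 − b²) × √(1 + a²/4), where b is the mediator slope and the within-arm outcome SD is 1. With total 0.33 SD and half direct:

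- a = 0.50, b = 0.33: SE ≈ 0.1336 × 0.944 × 1.031 = 0.130; power ≈ Φ(0.165/0.130 − 1.96) ≈ 25%.
- a = 0.33, b = 0.50: SE ≈ 0.1336 × 0.866 × 1.014 = 0.117; power ≈ Φ(0.165/0.117 − 1.96) ≈ 29%.

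The simulation gives 25% and 29% for these two cases.

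**Step 3: the rule itself.** M = a·group + error; Y = direct·group + b·M + error; 10,000 trials per scenario, 112 per arm, two-sided 0.05. The gate is a significant group effect on Y and on M. The last column is the share of gate-passing trials in which the direct effect is non-significant, so that the rule says complete although a direct effect exists. Paired figures are for a = 0.33 and a = 0.50.

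| Total effect | Share direct | Pass the gate | Labelled complete |
|---|---|---|---|
| 0.33 SD | 50% | 54%, 68% | 64%, 65% |
| 0.33 SD | 75% | 52%, 67% | 37%, 37% |
| 0.374 SD | 50% | 62%, 78% | 58%, 62% |
| 0.374 SD | 75% | 58%, 77% | 32%, 33% |

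With 70% direct, further runs gave 42-43% at 0.33 SD and 36-38% at 0.375 SD. Across all runs the range was roughly 57-65% when half is direct and 36-45% when 70% is direct.

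**Step 4: sensitivity.**

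- Baseline explaining 25% of outcome variance (total 0.33 SD, a = 0.50): 61% when half is direct, 32% when 75% is direct.
- Baseline explaining 40% of outcome variance: about 25-55% when half is direct, 17-34% when 70% is direct.
- Total effect 0.50 SD (a = 0.50, no baseline adjustment): 44% when half is direct, 18% when 75% is direct.
- Also requiring a significant Sobel test (total 0.33 SD, 75% direct): the rate rises from 37% to 42-48%.

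**The case against.** The strongest reply is that the label would not stand alone. The percent of variation mediated would be reported beside it, Sobel's test is planned, and the Preliminary Analysis section plots change in outcomes against change in mediators. The section also refers to later developments of the method. It is true that readers would see more than a bare label. But none of these quantities alters the verdict, and the sentences that follow the reference to later work fix the significance rule. Sobel's test concerns the indirect effect and says nothing on whether the direct effect is zero.

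A second reply is that the rates depend on assumptions. This stands. The planned outcome models adjust for the baseline score, and adjustment lowers the rates, as does a larger total effect. The figures are a range, not a prediction.

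Four stronger readings are tempting, and the article does not support them:

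- *The rule declares complete mediation whenever the direct effect is non-significant.* It applies only after the gate is passed, and the rates above are conditional on that.
- *Sobel's normal approximation fits badly at this size.* Its 95% intervals covered the true indirect effect in about 93-96% of simulated trials.
- *The plan pairs a week-10 mediator with a week-10 outcome, so direction cannot be told.* The mediators are indeed measured only at baseline and week 10 (for self-efficacy, "source: patient baseline and 10 week surveys). The Cancer Behavior Inventory"). But Mediation Analysis does not fix the outcome's time point, Hypothesis Testing plans week-14 models, and service use comes from chart review.
- *The gate on the total effect is an error.* The section asks whether improvements are mediated, which presupposes an improvement. Keeping or dropping the gate is a debatable choice.

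**Conclusion.** The point holds for the complete/partial verdict rule. The rule infers absence of a direct effect from non-significance, at a sample size chosen for the larger total effect, and against a hypothesis of partial mediation. With 112 per arm, a total effect of 0.33-0.375 SD and a mediator effect of 0.33-0.50 SD, the false label is the majority result without baseline adjustment when half the effect is direct. It remains common when 70% is direct. Even with a baseline score explaining 40% of outcome variance, between about one in six and one in two gate-passing trials would be mislabelled across these scenarios.

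A reader might infer that a false label would drive redesign of the programme. The article's Discussion ties redesign to increased caregiver burden, so that consequence is speculative. The damage is confined to the conclusion on Hypothesis 1b. This should be changed, but it does not threaten the main result.

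**What to change.** In Mediation Analysis, delete the two sentences that assign complete or partial mediation by significance. Instead report, for each mediator and outcome:

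- the indirect effect (product of coefficients) with a bootstrap 95% confidence interval;
- the direct effect with a 95% confidence interval;
- the proportion mediated with a bootstrap 95% confidence interval.

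Adjust the models for the baseline mediator and, where it was measured, the baseline outcome. Base any statement on Hypothesis 1b on these intervals.

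As a supportive analysis, add a model with the week-10 mediator and the week-14 outcome. Symptom severity and physical functioning are already collected at week 14, and this helps with temporal order. It need not replace the planned analysis, because the article defines the primary effect at week 10.

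The cost is a change of wording and some analysis code. The small downside is that the report will give intervals, which may be wide, in place of a clear verdict.

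### The mediation rule reads a non-significant direct effect as complete mediation, a conclusion that this trial's size often cannot support

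*Protocol article*

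**What the plan says.** Hypothesis 1b (protocol article, Background) predicts that the intervention effect "will be partially mediated by improved patient self-efficacy and actualized social support".

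The Mediation Analysis section adopts the causal-steps (Baron–Kenny) approach, in three parts:

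- An entry condition: "To establish mediation, the study group effect has to be significant in all but the last model". The total effect and the group-to-mediator effect must therefore both be significant.
- Two verdicts from the last model, which contains both group and mediator. One is "If in the last model the study group effect is not significant, then we will conclude that complete mediation has occurred". The other is "If in the last model the study group effect is reduced, but is still significant, then we will conclude that partial mediation has occurred".
- A further test and a summary: "To test for mediation, Sobel's test will be carried out, and percent of variation in outcomes mediated by patient or caregiver mediators will be determined".

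The Sample Size Calculation section sizes the trial on the total effect: "Testing the primary outcome using two sided t-testing will require at least 224 dyads", with 80% power claimed for "a difference as small as 0.33 standard deviations" at 0.05. It applies the same 0.33 SD to social support.

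**The concern.** A p-value of 0.05 or more for the direct effect means that the data have not shown one. It does not mean that the direct effect is zero. The rule sets no margin and no confidence-interval condition, so an imprecise estimate is enough to earn the stronger verdict.

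The trial's size makes this more than a formality. Under partial mediation with direct and indirect effects in the same direction, the direct effect is only part of the total effect on which the sample size rests. A true partial mediation can therefore be labelled complete because the trial is too small to see the remainder, and a smaller sample makes that label more likely.

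At stake is what readers are told about mechanism. A verdict of complete mediation says that self-efficacy or social support accounts for the whole benefit and that caregiver engagement works in no other way.

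**Working it through.** **1. The plan's own figure.** Inputs from Sample Size Calculation: 112 per arm, 0.33 SD, two-sided 0.05. The noncentrality is 0.33 × √(112/2) = 2.47 and the critical t on 222 df is 1.97, so power is about P(Z > 1.97 − 2.47) = 69%, not 80%. A baseline–outcome correlation of about 0.48 would restore 80%: 0.33/√(1 − 0.48²) = 0.376, noncentrality 2.81, power about 80%. No correlation is stated. The mediation rule is therefore checked both without baseline adjustment and with an assumed correlation of 0.5. The sample-size discrepancy itself is a separate matter.

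**2. Direct effect.** Direct effect = 0.33 × (1 − share mediated). This gives 0.231 SD at 30% mediated and 0.165 SD at 50%.

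**3. Power in the last model.** A plain two-sample t-test on these differences would give 41% and 23%, but the last model also contains the mediator. Assume a group-to-mediator effect a = 0.33 SD (given for social support only), within-arm SDs of 1, and mediator slope b = share × 0.33/a, so b = 0.30 or 0.50. With baseline correlation r, the residual variance is 1 − b² − r², and

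Var(direct) ≈ residual variance × (2/112 + a²/222) = residual variance × 0.01835.

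- 30%, r = 0: residual variance 0.91, SE 0.129, ratio 0.231/0.129 = 1.79, power about 43%.
- 50%, r = 0: residual variance 0.75, SE 0.117, ratio 1.41, power about 29%.
- 30%, r = 0.5: residual variance 0.66, SE 0.110, ratio 2.10, power about 55%.
- 50%, r = 0.5: residual variance 0.50, SE 0.096, ratio 1.72, power about 40%.

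Simulation gives 42%, 29%, 54% and 41%.

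**4. The whole rule, simulated.** Each trial must show a significant total effect and a significant group-to-mediator effect. Among those that do, we count how often the direct effect has p ≥ 0.05. Every such verdict is wrong by construction.

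| Truly mediated | Baseline correlation | Last-model power | 'Complete' among trials passing the earlier steps |
|---|---|---|---|
| 30% | 0 | 42% | 45% |
| 50% | 0 | 29% | 64% |
| 30% | 0.5 | 54% | 37% |
| 50% | 0.5 | 41% | 54% |

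Separate runs of the same settings agree to within about 3 percentage points. Between 52% and 63% of trials pass the earlier steps, so the error per trial started is about 0.45 × 0.52 = 23% at 30% mediated and 0.64 × 0.53 = 34% at 50%. The baseline-adjusted runs give nearly the same per-trial figures.

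**5. Does Sobel's test help?** Requiring a significant Sobel test as well leaves the conditional rates at about 45% and 63% without baseline gain, and 40% and 57% with a baseline correlation of 0.48. Sobel's test asks whether the indirect effect differs from zero. It says nothing about whether the direct effect is zero.

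**6. Sensitivity.**

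- Total effect 0.5 SD, 112 per arm: roughly 1% to 42% of trials passing the earlier steps, for mediator effects of 0.33 to 0.5 SD with and without baseline adjustment. With a mediator effect of 0.8 SD, half mediated and no baseline gain, it reaches 53%.
- All 150 per arm analysed, baseline correlation 0.5, total and mediator effects 0.33 SD: 29% and 46% at 30% and 50% mediated.

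**The case against.** The strongest case on the other side has four parts.

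- **The frequency rests on assumptions.** The article gives no mediated share, no expected effect on self-efficacy and no baseline correlation. It describes 0.33 SD as the smallest detectable difference, not the expected one. This stands. The rates are conditional illustrations at the trial's design effect, and at 0.5 SD they can become negligible.
- **The rest of the paragraph softens the harm.** Sobel's test addresses the indirect effect directly, and the percent mediated would appear beside the label. In simulated trials labelled complete, the median estimated share was about 0.4 when the truth was 0.3 and about 0.6 when it was 0.5, so an attentive reader would see a number at odds with the word. This stands as mitigation. The percent mediated does not alter the verdict, however, so the report could carry both a partial share and a claim of complete mediation.
- **The approach is established, and an unseen analysis plan may add intervals.** Added detail would not repair a decision rule that is already fixed and wrong as written.
- **The stakes are limited.** The rule is a secondary label and leaves the primary comparison untouched. This stands.

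A reader might go further and infer that the rule contradicts Hypothesis 1b. It does not: a rule that can return either verdict is compatible with a prediction of partial mediation. A reader might also take the direct effect to be smaller than the total by definition. That holds only when direct and indirect effects have the same sign. A mediator acting in the opposite direction would make the direct effect the larger of the two.

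**Conclusion.** The rule is unsound as written: it accepts a null hypothesis on non-significance alone, and nothing else in the article corrects it. With 112 per arm, total and mediator effects of 0.33 SD and 30% to 50% truly mediated, about 37% to 64% of the trials that reach the rule would be wrongly labelled complete, or about 23% to 34% of all trials. These figures assume that direct and indirect effects share a sign. They also rest on mediator effects and baseline correlations that the article does not give for self-efficacy. The documents do not support saying that the mislabel will usually occur whatever the true effect, or that the trial's main conclusion is at risk. The point deserves correction because it governs how a named hypothesis is reported.

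**What to change.** In Mediation Analysis, delete the complete and partial verdicts that depend on significance of the direct effect. Report the indirect and direct effects, each with a 95% confidence interval, beside the percent mediated already planned. Judge Hypothesis 1b on the indirect-effect interval. Use the word 'complete' only if the direct-effect interval lies within a small margin fixed in advance, or else drop the word.

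The cost is one reworded paragraph and no new data. What is lost is a simple label, and if a margin is used it must be justified beforehand.

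### Sobel's test, on top of a required significant total effect, is conservative for the small-to-moderate paths planned here; test Hypothesis 1b with an interval for the indirect effect and drop the total-effect condition

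*Protocol article*

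**What the plan says.** Hypothesis 1b (Background) is a named hypothesis: the intervention's effect on symptom severity, physical functioning and service use "will be partially mediated by improved patient self-efficacy and actualized social support".

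The Mediation Analysis section fixes two elements. The first is the Baron-Kenny sequence: "To establish mediation, the study group effect has to be significant in all but the last model". The models are outcome on group, mediator on group, and outcome on mediator and group, so the total effect and the group-to-mediator effect must both be significant. The second is the formal test: "To test for mediation, Sobel's test will be carried out". The section mentions later developments of the approach, but the article names no bootstrap, product-distribution or joint-significance method.

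The Sample Size Calculation section supplies the scale: "will require at least 224 dyads (patients and caregivers) to complete the study (112 per arm"), with 0.33 SD as the difference to detect in symptom severity and in social support. Actualized social support is also one of the two mediators. No power or error rate is stated for the mediation test.

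**The concern.** The indirect effect is the product of two paths: group to mediator (a) and mediator to outcome (b). It is zero if either path is zero. Sobel's test divides the estimated product by its delta-method standard error and refers the ratio to a standard normal. That reference is adequate when one path is zero and the other is many standard errors from zero. It is poor when the non-zero path is only two or three standard errors away, because the product is then far from normal and the test rejects too rarely.

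What is at stake is the chance of showing a real mechanism. The error is towards caution, so false claims of mediation are not the risk. The risk is that mediation by self-efficacy or social support is reported as unproven when the same data could have shown it.

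**Working it through.** **Inputs.** From the Sample Size Calculation section: 112 completers per arm, two-sided 0.05, a = 0.33 SD for social support. The same a is assumed for self-efficacy, for which no effect is given. Assumptions, because the protocol is silent: slope b (shown over a range), the direct effect, unit residual SDs, linear models, complete data, no baseline covariate.

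**The plan's own figure.** A two-sided unadjusted t-test at 0.33 SD with 80% power needs 145 per arm; 112 per arm gives 69%. The 112 is close to a one-sided calculation (114 per arm), or fits a baseline-outcome correlation of about 0.47. Attrition reproduces: 224/0.75 = 299, about 300. The mediation point does not depend on this discrepancy.

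**Algebra.** With z_a and z_b the two path statistics,

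z_Sobel = ab / √(a²·se_b² + b²·se_a²) = z_a·z_b / √(z_a² + z_b²).

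This is always smaller in size than the weaker of z_a and z_b. Sobel therefore cannot reject unless both paths already exceed 1.96, and then it asks for more. Here se_a = √(2/112) = 0.1336, so the expected z_a is 0.33/0.1336 = 2.47. Setting z_Sobel = 1.96 gives z_b = 1.96 × 2.47 / √(2.47² − 1.96²) = 3.22. At the planned mediator effect, the second path must reach p of about 0.0013.

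**Error rate, simulated (N = 224, direct effect zero; 20,000 trials, 4,000 for the interval).**

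| True paths | Sobel | Joint significance | Monte Carlo product interval |
|---|---|---|---|
| a = 0, b = 0 | 0.01% | 0.3% | 0.1% |
| a = 0.33, b = 0 | 0.7% | 3.5% | 3.2% |
| a = 0.5, b = 0 | 1.8% | 4.7% | 4.4% |
| a = 1.2, b = 0 | 4.6% | 5.1% | 4.6% |
| a = 0, b = 0.3 | 2.7% | 4.8% | 5.1% |
| a = 0, b = 0.59 | 4.8% | 5.3% | 4.8% |

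At N = 300 with a = 0.33 and b = 0, Sobel rejects in 1.0%.

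**Power of each test on its own (N = 224, a = 0.33).**

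| Assumed slope b | Sobel | Joint significance | Product interval |
|---|---|---|---|
| 0.14 | 17% | 38% | 35% |
| 0.2 | 35% | 58% | 54% |
| 0.3 | 58% | 69% | 71% |
| 0.39 | 64% | 69% | 70% |
| 0.59 | 68% | 69% | 70% |

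Repeat runs gave 35-37% against 54-59% at b = 0.2, and 57-59% against 67-71% at b = 0.3. Joint significance levels off near 69% because that is the power of the group-to-mediator path itself.

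**Adding the total-effect requirement.** The total effect is direct + a·b, with standard error √(1 + b²) × 0.1336. At b = 0.2, a·b = 0.066 and the standard error is 0.1363.

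- No direct effect: 0.066/0.1363 = 0.48, so the total effect is significant in about 8% of trials.
- Direct effect 0.1 SD: 0.166/0.1363 = 1.22, about 23%.
- Total effect 0.33 SD: 0.33/0.1363 = 2.42, about 68%.

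Power when the total effect must also be significant (a = 0.33), Sobel against joint significance:

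| Setting | b = 0.2 | b = 0.3 |
|---|---|---|
| No direct effect | about 4% v 5% | 8% v 9% |
| Direct effect 0.1 SD | 9-10% v 14-15% | 20-21% v 23% |
| Total effect 0.33 SD | 26-27% v 40-42% | 42% v 49% |

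Replacing Sobel while keeping the requirement therefore gains about 1-15 points at b = 0.2 and 1-7 at b = 0.3. In the middle row at b = 0.2, changing both parts moves power from about 10% to 54-58%.

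**The bootstrap (N = 224, 1,200 trials, 500 resamples).** Null rejection was 0.1% at (a, b) = (0, 0), 3.6% at (0.33, 0), 5.2% at (0.5, 0), 6.2% at (0, 0.3) and 4.7% at (0, 0.6). The Monte Carlo standard error is √(0.05 × 0.95/1200) = 0.6 points. Power was 54% against 34% for Sobel at (0.33, 0.2), and 70% against 59% at (0.33, 0.3).

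**The case against.** Four points can fairly be made for the plan.

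- **The conservatism is not a property of 224 completers.** A reader might infer that Sobel's error rate is far below 5% whatever the truth. It is not: with one strong path it is 4.6-4.8%, and at slopes of 0.39 or more the power loss is about 5 points or less. This stands and limits the point to small-to-moderate paths.
- **Sobel is not used alone.** A reader might infer that replacing it would recover about 20 points. Under the plan's full rule it would not, because the total-effect requirement is in most of the settings tried the larger cause of missed mediation. This stands, and it is why the fix has two parts.
- **The slope is assumed.** It is, and no value in the article settles it. The planned mediator effect of 0.33 SD is the only path with a figure.
- **The error is on the safe side and the hypothesis is not primary.** Also true. It cannot raise false claims of mediation above 5%, and the 10-week symptom comparison is unaffected.

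One might add that without a total effect there is nothing to mediate. But non-significance is weak evidence of no effect: at a true 0.33 SD an unadjusted comparison of 112 per arm misses it about 31% of the time (100% − 69%). None of this favours Sobel, which had lower power than the alternatives in every alternative setting simulated, while they held at or near 5%.

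**Conclusion.** The point holds for small-to-moderate paths, which is where the plan's own mediator effect places the trial. At a = 0.33 SD and 224 completers, Sobel's error rate is about 0.7% when the mediator-outcome path is zero. Used alone it loses roughly 20 points of power at an assumed slope of 0.2, about 10 at 0.3, and 1-2 at 0.6. The total-effect condition in the same section costs more than Sobel does in most settings tried, so the two must be dealt with together.

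The figures rest on linear models with unit residual SDs, complete data and no baseline adjustment, and on reading the section as requiring both the Baron-Kenny conditions and a significant Sobel test. They apply to continuous outcomes such as symptom severity and were not run for service use. This is a near-costless improvement to a named secondary hypothesis; it does not threaten the trial's main result.

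**What to change.** In the Mediation Analysis section:

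1. Replace Sobel's test with a 95% percentile-bootstrap or Monte Carlo (distribution-of-the-product) confidence interval for the indirect effect, from the baseline-adjusted mediator and outcome models. Judge Hypothesis 1b by whether that interval excludes zero.
2. In the same edit, state that a significant total effect is no longer required to establish mediation. The Baron-Kenny steps may stay as description. Without this sentence the section would hold two decision rules that can disagree, and most of the gain would be lost.

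The cost is two sentences and a little computing. No new data are needed, and error stayed at or near 5% in the settings simulated.
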